##### Gut and nasal microbiota analysis (secondary endpoints)

2.3.3.2

The stool and nasal samples will be stored at −80 °C until genomic DNA extraction. The Maxwell® RSC Faecal Microbiome DNA Kit and Maxwell® RSC Pathogen Total Nucleic Acid Kit will be employed for DNA isolation from stool and nasal samples, respectively, using a Maxwell RSC automated extractor (Promega s.r.l., Milan, Italy), according to the manufacturer’s recommendations. The quality and quantity of gDNA will be assessed by TapeStation 4,200 system (Agilent, Santa Clara, CA, USA) and Qubit 4 fluorometer (Invitrogen, Waltham, MA, USA). Afterwards, the sequencing libraries will be prepared by using the MICROLAB STARlet NGS UV automated liquid handling station (Hamilton Italia Srl, Agrate Brianza, Italy), following an NGS metabarcoding approach. The 16S Metagenomic Sequencing Library Preparation protocol will be employed for the amplification of the V3-V4 hypervariable regions of the 16S rRNA gene and indexing by dual Nextera® XT indexes (Illumina, San Diego, CA, USA). All libraries, quantified by the Qubit 4 fluorometer and pooled at equimolar concentrations, will subsequently be sequenced using the Illumina NextSeq1000 platform through a 2x300bp paired-end run.

Raw sequencing reads will be processed following a specific pipeline, involving the merging of two paired reads overlapping, generating a single fragment covering the whole V3-V4 regions, the trimming and filtering of low-quality reads and the grouping to Amplicon Sequence Variants (ASVs) by the DADA2 denoising pipeline (50). Taxonomic classification will be performed by the RDP classifier (51) against the latest release of the SILVA reference database (52).

Biodiversity will be estimated by calculating the alpha-diversity for each sample using different metrics, such as Shannon’s entropy index, observed species, Chao1 index and Faith’s phylogenetic diversity index. Pairwise similarity between microbial profiles will be assessed using the unweighted and weighted implementations of the UniFrac distance (53). Microbial composition will be expressed as the relative abundance of taxa at different levels, from phylum to genus. Due to the lower complexity of the nasal microbiota, its composition will be characterised down to the species level for some of the most abundant genera (e.g., *Corynebacterium, Moraxella, Haemophilus*).

##### Neurofilament proteins and pro-and anti-inflammatory cytokine levels assessment

2.3.3.3

Human neurofilament light chain protein (NfL) levels will be quantified from plasma samples using the Simple Plex assay (ProteinSimple, California, USA) on the Ella microfluidic immunoassay platform (ProteinSimple, California, USA), following the manufacturer’s protocol (54). The Ella device will be calibrated using the in-cartridge factory standard curve, and plasma samples will be prepared with a 1:2 dilution in the provided Sample Diluent (ProteinSimple, California, USA) (54).

Each sample will be analysed in a single well, as the Simple Plex platform automatically performs triplicate assays within the microfluidic system (54). The lower limit of quantification (LLOQ) for this assay is 2.70 pg./mL, and the upper limit of quantification (ULOQ) is 10,290.00 pg./mL (54).

Serum concentrations of various cytokines and growth factors, including interleukin (IL)-1β, IL-2, IL-4, IL-6, IL-10, IL-12, IL-17, IL-22, and IL-23, as well as transforming growth factor beta (TGF-β), granulocyte-macrophage colony-stimulating factor (GM-CSF), tumour necrosis factor-alpha (TNF-α), and interferon-gamma (IFN-γ), will be measured. These cytokines will be quantified in picograms per millilitre (pg/mL) using the Simple Plex assay (R&D Systems) and commercial enzyme-linked immunosorbent assay (ELISA) kits, including CXCL10 measurements where applicable (55).

##### Vitamin D levels assessment

2.3.3.4

For each patient, serum 25(OH)D concentrations will be measured using the Elecsys® Vitamin D total III assay (Roche Diagnostics, Mannheim, Germany) on a Cobas Pure integrated analyser (Roche Diagnostics). The assay is an electrochemiluminescence competitive binding immunoassay designed for the quantitative determination of total 25(OH)D (including 25(OH)D₂ and 25(OH)D₃) in human serum or plasma (lithium heparin, K₂-EDTA). For this study, fasting venous blood samples will be collected, allowed to clot at room temperature, and centrifuged at 3,000 × g for 10 min to obtain serum, which will be stored at −80 °C until analysis.

From an analytical perspective, the assay demonstrates a functional sensitivity of 4.01 ng/mL (10.03 nmol/L), with a CV of 18.5%. The response is linear across the full measuring range; on the Cobas e 601 platform, analytically comparable to the Cobas Pure analyser, linearity has been verified between 1.67 ng/mL (4.18 nmol/L) and 133 ng/mL (332.5 nmol/L), with deviations from linearity consistently below ± 2 ng/mL (5.0 nmol/L) or 10% bias.

According to the manufacturer’s validation data, the Elecsys® Vitamin D total III assay, when performed on the Cobas Pure automated immunoassay analyser, has a Limit of Blank (LoB) of 2.0 ng/mL (5.0 nmol/L), corresponding to the highest measurement expected in the absence of analyte. The Limit of Detection (LoD) is 3.0 ng/mL (7.5 nmol/L), defined as the lowest concentration that can be distinguished from the LoB with 95% probability. The Limit of Quantitation (LoQ) is 6.0 ng/mL (15.0 nmol/L), representing the lowest concentration measurable with acceptable precision, defined as a coefficient of variation not exceeding 20%.

To evaluate the vitamin D status of each patient, we will adopt the 25-OH-D cut-off values proposed by SIOMMS (56). The severe deficiency will be reported for 25-OH-D < 10 ng/mL levels (<25 nmol/L); deficiency for 25-OH-D between 10 and 20 ng/mL (25–50 nmol/L) levels; insufficiency for 25-OH-D between 20 and 30 ng/mL (50–75 nmol/L) levels; adequacy for 25-OH-D between 30 and 100 ng/mL (75–125 nmol/L) levels and toxicity for 25-OH-D > 100 ng/mL (>125 nmol/L) levels (57).

### Statistical analysis

2.4

#### Sample size calculation

2.4.1

Regarding the background for the sample size calculation, to identify a small number of miRNAs to be validated as diagnostic MS-associated miRNA profiles in RT-qPCR on serum samples, a bioinformatic analysis was preliminarily conducted and described in section 2.2.3 Internal exposome variables.

As for the sample size calculation, to validate variation among the selected MS diagnostic miRNA, in response to urban air pollution, urbanisation, lifestyle and QoL components of the external exposome, the differential expression (ΔCT) for each miRNA will be considered as the endpoint measure. To compare the mean difference of ΔCT for each miRNA among exposure groups and to include the possible modulating effect in terms of accommodating covariates, negative binomial generalised linear models (GLM) will be used. Sample size has been calculated accordingly (58) through an estimating procedure based on a representative exemplary dataset created for a single miRNA comparison among two groups of pwMS defined by a specific external exposure variable and including a vector of covariate variables for the miRNA sample. The alternative hypothesis that the logarithm of miRNA fold change is different from zero against the null hypothesis of a log fold change equal to zero, by the likelihood ratio test statistic, will also be tested.

The minimum number of pwMS necessary to achieve 80% of power, considering a desired minimum miRNA fold change between 1.1 and 4.5, was 168. Therefore, 200 eligible pwMS who meet the inclusion criteria and sign the informed consent will be included in the study, considering a 15% dropout at the blood sampling stage.

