### Objectives

2.1

EXPosome, Oxidative Stress and InflammaTION in Persons with MS (EXPOSITION) study is a cross-sectional research initiative, designed to evaluate the variation of candidate biological biomarkers of OS and inflammation in response to the external exposome in pwMS (Figure 1).

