**Figure 1 fig1:**
[figure not shown]
External exposome and biological responses in multiple sclerosis: the EXPOSITION approach. The diagram depicts the urban exposome domains hypothesized to influence MS. The External Exposome (beige arc) summarises the broad environmental context including urbanization and air quality typical of Po Valley settings. The External Specific Exposome (green arc) represents individual-level lifestyle and behavioural factors, including smoking habits, quality of life, dietary supplement use, physical activity, and nutrition. The Internal Exposome (blue arc) comprises measurable biological mediators and effect markers, including gut microbiota, neurofilament, circulating cytokines, and microRNA. Bidirectional arrows indicate dynamic interactions across domains, converging on MS pathophysiology (central illustration).

Particularly, the primary objective of the EXPOSITION study is to investigate the variation of microRNA (miRNA) expression, in response to general external exposome (urban air pollution and urbanization), as well as occupational and lifestyle external exposome components in pwMS, controlling for other validated biomarkers (e.g., serum pro- and anti-inflammatory cytokine levels, serum neurofilaments levels, serum vitamin D levels), gender, age, anthropometric measurements, and medical history.

The secondary objective is to investigate the variation of the gut and nasal microbiota composition as candidate biological biomarkers of OS and inflammation, in response to the exposome components and other variables included in the primary objective methodological framework. The microbial profiles will be evaluated in terms of (i). Biodiversity (alpha-diversity), estimating the number of taxa in each sample and statistically comparing estimates across the experimental groups; (ii). Composition (beta-diversity), evaluating the pairwise similarity among the samples and clustering them according to their distances; (iii). Bacterial groups (relative abundances), evaluating whether a bacterial taxon is significantly increased or depleted in pwMS belonging to the different exposome profiles under investigation.

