#### Social, demographic and clinical data

2.3.1

Social and demographic data includes age, sex, ethnicity, date and place of birth, civil status, education level, employment status, and current residence address. Clinical data includes information on disease onset and diagnosis (date of onset, date of diagnosis, presence of oligoclonal bands), disease duration, MS phenotype, date of last relapse, information on the most recent MRI (new/enlarging T2-weighted lesion, Gadolinium enhancing lesions) and No-evidence of disease-activity status (NEDA3), information on disease-modifying treatments (DMT-number and type of previous treatments, and reasons for discontinuation, start date of the ongoing treatment) as well as of symptomatic treatments related to MS or any other clinical condition. The level of clinical disability will be quantified using the Expanded Disability Status Scale (EDSS) (27). All the data will be anonymised and collected in RedCAP.

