##### Quality of life

2.3.2.4

QoL will be evaluated by Multiple Sclerosis Quality of Life-29 (MSQOL-29) (38), a multidimensional health-related QoL measure that combines both generic and MS-specific items into a single instrument. The questionnaire consists of 29 items, divided into 7 subscales related to physical functioning, pain, emotional well-being, energy, cognitive function, health stress, sexual function, change in health, social function, health perception and overall QoL (38).

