For instance, the role of the Epstein–Barr virus in eliciting aberrant immune responses, the impact of vitamin D deficiency on immune modulation, and the exacerbation of OS and inflammation by air pollutants such as PM2.5 all highlight specific pathways for therapeutic intervention (11, 14, 64). These insights could lead to targeted strategies, such as antioxidant therapies, pollution-control policies, and personalised lifestyle interventions. Additionally, understanding the mechanisms by which exposome factors compromise the blood–brain barrier or promote neurodegeneration could pave the way for therapies aimed at preserving CNS integrity and halting disease progression. This approach also facilitates patient stratification based on exposure profiles, enabling the development of more personalised prevention and treatment plans.

The anticipated endpoints of the EXPOSITION study are expected to significantly expand our understanding of the environmental triggers of MS and provide a foundation for developing targeted interventions and precision medicine strategies. By focusing on modifiable environmental factors, these approaches have the potential to curb disease progression, ultimately improving the QoL for individuals with MS. The study’s findings could also inform broader public health policies, emphasising the importance of addressing environmental exposures to reduce the overall burden of MS. Furthermore, the methodologies employed in this study could be adapted for investigating other NCDs, thereby extending their impact beyond MS.

The results are also anticipated to empower patients by elucidating the extent to which external exposome factors influence MS, fostering better disease comprehension.

Additionally, the findings will provide actionable evidence to policymakers, supporting the development of interventions targeting external exposome through healthcare systems and related organisations; this could include strategies such as public health initiatives, urban planning adjustments, and institutional measures designed to mitigate harmful environmental exposures.

Despite its groundbreaking approach, the EXPOSITION study has certain limitations.

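### MSQOL-29, a partly MS-specific health-status scale, is classed as an external exposure to which miRNA responds, so disease severity can be reported as an exposome effect

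*Protocol article*

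**What the plan says.** Three places give quality of life (QoL) the role of an exposure.

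- Section 2.3.2.4 (Quality of life) sits under 2.3.2, the heading for general and specific external exposome factors.
- The Figure 1 legend puts it in the external specific exposome, among "individual-level lifestyle and behavioural factors, including smoking habits, quality of life, dietary supplement use, physical activity, and nutrition".
- Section 2.4.1 has the miRNAs varying "in response to urban air pollution, urbanisation, lifestyle and QoL components of the external exposome".

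Section 2.3.2.4 describes the instrument, MSQOL-29, as "a multidimensional health-related QoL measure that combines both generic and MS-specific items into a single instrument". Its listed content is "physical functioning, pain, emotional well-being, energy, cognitive function, health stress, sexual function, change in health, social function, health perception and overall QoL".

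Two other places point the other way.

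- The Discussion says of approaches aimed at modifiable exposures that "these approaches have the potential to curb disease progression, ultimately improving the QoL for individuals with MS".
- The primary objective in 2.1 names the exposures as the "general external exposome (urban air pollution and urbanization), as well as occupational and lifestyle external exposome components in pwMS". QoL is not named.

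On design, 2.1 says the "study is a cross-sectional research initiative".

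On severity, 2.3.1 collects EDSS, date of last relapse, MRI activity and NEDA3 status. Adjustment is described in general terms: clinical covariates (Figure 2 legend), medical history, neurofilaments and cytokines (2.1), and confounders plus the validated biomarkers (2.4.5 e). EDSS is not named as an adjuster in the miRNA models.

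**The concern.** An external exposure should be an input to the patient. Physical functioning, pain, energy, cognition, sexual function, change in health and health perception are states of the patient, and in established relapsing–remitting MS they can follow disability and disease activity. The five miRNAs were selected because they differ between MS and healthy samples (2.3.3.1), so they may follow disease activity too. If both do, severity is a common cause: MSQOL-29 and a miRNA will be associated even when no exposure acts on the miRNA, and a single assessment cannot separate that from a response of miRNA to QoL.

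The classification also matters beyond the single-exposure models. Section 2.4.2 plans exposure indices built from latent factors of the external exposome. Section 2.4.5 plans clustering of individuals by exposure pattern, PCA or FAMD, and lasso or elastic net selection of the most informative exposures. A health-status scale in that set lets an index, cluster or selected predictor carry severity under an exposure label.

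**Working it through.** **The documents side by side.** QoL is an exposure in 2.3.2.4, Figure 1 and 2.4.1, is downstream of progression in the Discussion, and is absent from the exposures named in the primary objective. The limitations in the Discussion do not address it. This inconsistency needs no arithmetic.

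**How large the effect could be.** The plan gives no figure for this point, so what follows is an illustration. From the documents: n = 168 (the minimum in 2.4.1) and n = 200 (the recruitment target). Everything else is assumed: a latent severity S; absolute correlation of QoL with S of 0.5 to 0.6; of a miRNA with S of 0.3 to 0.4; no effect of QoL on miRNA; a two-sided 5% test on the raw p-value of one miRNA.

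1. Association with no adjustment: r = r(QoL,S) × r(miRNA,S).
   - Low: 0.5 × 0.3 = 0.15. High: 0.6 × 0.4 = 0.24.
2. Rejection probability by Fisher's z: z = atanh(r) × √(n − 3 − k), with k the number of adjusters; probability = Φ(z − 1.96) + Φ(−z − 1.96).
   - Low, n = 168: z = atanh(0.15) × √165 = 1.94, giving 49%.
   - High, n = 168: z = atanh(0.24) × √165 = 3.14, giving 88%.
3. Adjusting for a severity measure E with correlation e to S: partial r = (r − qm) / √((1 − q²)(1 − m²)), where q = e × r(QoL,S) and m = e × r(miRNA,S).
   - e = 0.7, low: q = 0.35, m = 0.21; (0.15 − 0.0735) / √(0.8775 × 0.9559) = 0.084; z = 1.07, giving 19%.
   - e = 0.7, high: q = 0.42, m = 0.28; (0.24 − 0.1176) / √(0.8236 × 0.9216) = 0.140; z = 1.81, giving 44%.
   - e = 0.9, low: q = 0.45, m = 0.27; 0.0285 / √(0.7975 × 0.9271) = 0.033; z = 0.43, giving 7%.
   - e = 0.9, high: q = 0.54, m = 0.36; 0.0456 / √(0.7084 × 0.8704) = 0.058; z = 0.75, giving 12%.

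| Adjustment | n = 168 | n = 200 |
|---|---|---|
| None | 49–88% | 56–93% |
| Severity measure with e = 0.7 | 19–44% | 22–51% |
| Severity measure with e = 0.9 | 7–12% | 8–13% |
| Perfect (e = 1) | 5% | 5% |

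4. Sensitivity to the weakest input. With a miRNA–severity correlation of 0.2 and n = 168, the rates are 25–34% unadjusted and 11–14% at e = 0.7. With 0.1, and QoL–severity 0.5, the unadjusted rate is 10%.

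**The case against.** The strongest reply is that the plan does adjust. Clinical covariates, medical history, neurofilaments, cytokines and confounders are all mentioned, good severity measures are collected, and which of them enter each model can properly be left to an analysis plan that is not shown. This stands as far as it goes. A reader might infer that severity is bound to be reported as an exposome effect, with rejection rates of 49–93%. The documents do not support that, because those rates belong to an unadjusted test that the protocol does not plan for the miRNA models. What survives is that real severity measures are imperfect, that no adjustment is described for the clustering or PCA, and that adjustment does not turn a health-status scale into an external input.

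A second reply is that 2.4.5 never names MSQOL-29. That is correct: it speaks of exposures, so the scale's entry into the clustering, PCA and lasso is inferred from its classification, though the inference is strong. It would go too far to say that the clusters become severity profiles, since one instrument would have to dominate pollution, diet, activity, sleep, smoking and occupation.

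Third, a difference between patients and healthy people does not establish a gradient within relapsing–remitting patients. This is fair, and is why the lower correlations are shown. FDR q-values will also be reported beside the raw p-values, which the illustration ignores.

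Fourth, the language is not uniformly causal: the Figure 1 legend has bidirectional arrows, and 2.4.5 e speaks of association. This softens the directional wording of 2.4.1 but leaves QoL in the exposure set. Section 2.3.2.3 also lists QoL among the lifestyle variables, so the objective's lifestyle component might be read to cover it. However, 2.4.1 lists the two separately.

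Finally, psychosocial stress belongs to the protocol's own exposome framework. Section 2.3.2.3 lists stress and QoL together, and MSQOL-29 appears to be the only named instrument covering stress and emotional or social well-being. This stands and shapes the fix.

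**Conclusion.** The point holds as a misclassification with a material but conditional risk. The protocol assigns an exposure role to a scale that its own description makes a measure of health status and its own Discussion places downstream of progression. A QoL–miRNA or QoL–microbiota association, or an index, cluster or penalised selection containing QoL, can therefore partly reflect severity and be presented as an exposome effect.

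The size depends on correlations the documents do not give and on how well severity is adjusted for. On the assumed values it runs from close to the nominal 5%, with very good adjustment, to large excess rejection with none. Even perfect adjustment would not settle direction in a cross-sectional study. The pollution, urbanisation and occupational single-exposure models and the sample size are not called into question.

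**What to change.** 1. Take MSQOL-29 out of the external exposome set used for the primary single-exposure models, the exposure indices (2.4.2), the clustering and PCA or FAMD, and the penalised selection (2.4.5). Report it separately as a disease-status descriptor or an outcome.
2. If its stress, emotional or social subscales are wanted as psychosocial exposures, analyse them separately, adjusted for EDSS and the disease-activity measures already collected. Report them as associations without direction, and show the clustering and lasso results with and without them.
3. Align the Figure 1 legend, 2.3.2.4 and 2.4.1 with the primary objective in 2.1.

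The cost is wording and some additional analysis, with no new data and no change to the sample size. The real downside is that the stress and psychosocial domain leaves the main exposure set. Step 2 keeps it in view.

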A portion of serum samples will be collected and immediately frozen at −20 °C. After being transported, serum samples will be thawed, and the circulating RNAs will be extracted (Trizol, Thermo Fisher Scientific). After a step of miRNA-specific reverse transcription (TaqMan miRNA reverse transcription kit, Thermo Fisher Scientific; Mir-X miRNA First-Strand Synthesis Kit, Takara), the copy-DNA obtained will be used as the template for Real Time-qPCR analyses of selected miRNAs by Singleplex TaqMan miRNA assay reactions and/or in SybrGreen-based RTqPCR (SIC).

The method of Livak et al. (49) will be applied for the comparative analysis of the relative expression of the selected miRNAs in serum samples, considering different combinations of the external exposome variables.

Specifically, RT-PCR returns the number of cycles that the samples underwent before they were detected, reported as a value known as the Cycle Threshold (CT). The CT values vary logarithmically with expression levels. ΔCT values are calculated by subtracting the CT value of the endogenous control for a given sample (or the mean of the CT values of the endogenous controls if more than one exists) from the CT value of the gene for the given sample. The ΔΔCT is calculated by subtracting the ΔCT of an experimental sample from a control sample. Fold change is calculated by raising 2 to the power of the negative ΔΔCT value since CT values are related to the amount of miRNA or gene logarithmically. A statistical analysis will be applied to highlight the differences in the expression of each miRNA in the two populations.

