#### Exposome clustering, correlation and association analyses

2.4.5

a) *Clustering.* Clusters of individuals who share similar exposure patterns will be identified using hierarchical clustering.b) *PCA.* Principal component analysis will be used to reduce the dimensionality of the exposome (e.g., PCA standard, robust or FAMD for both categorical and continuous exposures).c) *Assess correlation structure.* Pearson, Spearman or Cramer coefficients, as appropriate, will be calculated to determine correlation structures between variables of the same exposome component. A correlation matrix and heatmap or Circos plot will be created.d) *Validated biomarkers’ behaviour in the pwMS sample (Neurofilament proteins, levels of pro- and anti-inflammatory cytokines, vitamin D level).* They will be tested for correlation with the miRNA relative expression and with alpha, beta diversity and relative abundances; they will also be tested for association with each exposure variable of the external exposome.e) *Single exposure association analysis with the primary endpoint.* To estimate the association between the external exposome and the expression of miRNAs (the primary endpoint), separate regression models (negative binomial, linear, or mixed-effects, depending on the outcome distribution) will be fitted, taking account of previous clustering, and adjusting for confounders and other modifiers of effect (including the validated biomarkers described above).f) *Single exposure association analysis with the secondary endpoints.* Gut and nasal microbiota data, as the secondary endpoint, will be analysed employing non-parametric statistical tests (e.g., Mann–Whitney, Kruskal-Wallis tests) for comparing alpha-diversity and relative abundances, whereas a permutational multivariate analysis of variance with F-ratios (“adonis”) will be used for beta-diversity comparison. Linear regression models will be employed to perform multivariate statistics on biodiversity and relative abundances, correcting estimates for confounders and modifiers of effect (including DMT type and dietary habits as MEDI-LITE and DII).g) *Apply multiple testing correction.* For each association tested, both raw *p*-values and FDR (Benjamini–Hochberg) q-values will be reported; if exposures are strongly correlated, the ENT-Bonferroni p-value will also be reported (59–61)h) *Variable selection (e.g., exposures).* The modelling procedure will identify a final set of predictors of miRNAs or microbiome variation, allowing for the simultaneous inclusion of multiple exposures within the same model. Variable selection will be performed using generalised multivariable linear models estimated via penalised maximum likelihood, applying either a lasso or elastic net penalty to determine the most informative exposures associated with the outcomes.

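### Section 2.4.1 assigns a negative binomial model to ΔCT, a continuous log2-scale difference, and derives 168 under it; section 2.4.5(e) leaves the model open, so the two must be reconciled

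*Protocol article*

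**What the plan says.** Section 2.3.3.1 defines the measure. Of the RT-qPCR cycle thresholds it says: "The CT values vary logarithmically with expression levels". It then says that "ΔCT values are calculated by subtracting the CT value of the endogenous control for a given sample" from the CT of the target, and that "Fold change is calculated by raising 2 to the power of the negative ΔΔCT value".

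Section 2.4.1 states that "the differential expression (ΔCT) for each miRNA will be considered as the endpoint measure". The contrast is a difference in means ("To compare the mean difference of ΔCT for each miRNA among exposure groups"), and the model is given in the same sentence: "accommodating covariates, negative binomial generalised linear models (GLM) will be used". The sample size follows from it: "Sample size has been calculated accordingly (58) through an estimating procedure based on a representative exemplary dataset". The test is a likelihood ratio test of a log fold change of zero. The result is 168 people for 80% power at a minimum fold change between 1.1 and 4.5, raised to 200 for 15% dropout.

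Section 2.4.5(e), which describes the association analysis of the primary endpoint, is looser: "separate regression models (negative binomial, linear, or mixed-effects, depending on the outcome distribution) will be fitted". Section 2.4.3 adds that biomarker distributions will be examined and skewed variables transformed.

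**The concern.** A negative binomial model describes non-negative counts. ΔCT is not a count. It is a difference of two cycle values, is not restricted to integers, and is negative whenever the target miRNA is detected earlier than the endogenous control.

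Three things follow if section 2.4.1 is applied as it stands.

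- **Fit.** The likelihood is undefined for any participant with a negative ΔCT.
- **Estimand.** Under a log link the coefficient compares mean ΔCTs as a ratio. The stated hypothesis concerns a log fold change, which on this scale is a plain difference in mean ΔCT.
- **Error rates.** Negative binomial variance cannot fall below the mean, while the variance of ΔCT has no necessary relation to its mean. Where SD² is below the mean, the model overstates the standard error.

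At stake are the model for the primary endpoint, the meaning of the reported fold change, and the only stated justification for the sample size.

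**Working it through.** **1. The plan's own figures.** Dropout: 168 / (1 − 0.15) = 197.6, so 198. The planned 200 is consistent with this (200 × 0.85 = 170).

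The 168 itself cannot be reproduced from the article, which gives no alpha, negative binomial mean, dispersion or group split, and states the effect as a range. Assume two equal groups of 84, two-sided alpha 0.05 and 80% power, so that (1.96 + 0.84)² = 7.85. The usual two-group approximation is

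n per group = 2 × 7.85 × (1/μ + φ) / (ln FC)².

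Solving for n = 84 gives 1/μ + φ = 0.049 at fold change 1.1 and 12.1 at fold change 4.5, a 249-fold spread. The range therefore does not identify one design.

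**2. What the coefficient would mean.** Fold change is 2 to the power −ΔΔCT, so a one-cycle fall in ΔCT is a twofold increase whatever the baseline (ln 2 = 0.69). The log-link coefficient for the same one-cycle fall is:

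| Baseline ΔCT | Log ratio of means |
|---|---|
| 3 | ln(2/3) = −0.41 |
| 6 | ln(5/6) = −0.18 |
| 10 | ln(9/10) = −0.11 |

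The size depends on the baseline and the sign is reversed. This needs no assumption about the SD.

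**3. Power if the negative binomial model were used.** ΔCT was simulated as normal with 84 per group and one group shifted down by 0.432 SD, which gives a linear model 80% power. There were 400 replicates per cell. The negative binomial likelihood ratio test profiled the dispersion and included the Poisson limit. All means and SDs are assumptions.

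| Mean ΔCT | SD 1 | SD 1.5 | SD 2 | SD 3 |
|---|---|---|---|---|
| 5 | 6% | 52% | 82% | cannot be fitted |
| 10 | 0% | 13% | 41% | 79% |
| 15 | 0% | 2% | 19% | 61% |

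Type I error was about 0 to 3%. Power is counted only in datasets without a negative value. Negatives occurred in 18% of datasets at mean 5/SD 1.5, 89% at mean 5/SD 2, 100% at mean 5/SD 3 and 16% at mean 10/SD 3.

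A closed form for SD² below the mean agrees: power ≈ 1 − Φ(1.96 × √mean / SD − 2.80). At mean 6, SD 1 this is 1 − Φ(4.80 − 2.80), about 2%. At mean 6, SD 2 it is 1 − Φ(2.40 − 2.80), about 66%. As SD² approaches the mean it approaches 80%.

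**4. What 168 gives under a linear model.** Detectable shift = SD × √(2 × 7.85 / 84) = 0.432 SD cycles, and fold change = 2^(0.432 SD).

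| Assumed SD | Detectable fold change | Power at fold change 1.1 | Total N for fold change 1.1 |
|---|---|---|---|
| 0.5 | 1.16 | 43% | 416 |
| 1 | 1.35 | 14% | 1,662 |
| 1.5 | 1.57 | 9% | 3,738 |
| 2 | 1.82 | 7% | 6,644 |

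For fold change 2, the total N needed at the same SDs is 8, 32, 72 and 126, all below 168.

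**The case against.** The strongest reply is that section 2.4.5(e) is where the primary association model is specified, and it selects the model by outcome distribution. Anyone who looks at a continuous ΔCT with negative values would be led to the linear option, and section 2.4.3 provides for checking distributions. This stands in part. A reader might infer from section 2.4.1 that the primary analysis is fixed as negative binomial; the article does not support that. But ΔCT is never a count, so the negative binomial has no place among the options, and section 2.4.1 names it without qualification.

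A reader might also infer that most of the power will be lost. That is not supported either. The article gives no mean or SD for ΔCT, and the calculated loss runs from nearly everything (SD² far below the mean) to nearly nothing (SD² near or above it).

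Third, a reader might infer that 168 came from fitting a negative binomial model to ΔCT values. The article does not say whether the exemplary dataset held counts or ΔCT, and the method it cites is not reproduced. A hypothesis on log fold change would be coherent for counts. What can be said is narrower: 168 was derived under a count model, and nothing in the article justifies carrying its 80% power over to a mean difference in ΔCT.

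Finally, this is a condensed article on an observational study, and some detail belongs elsewhere. But the point is not missing detail: the article states a model that does not suit the endpoint it defines.

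**Conclusion.** The point holds in this form. Section 2.4.1 pairs ΔCT with a count model that is undefined for negative values and whose usual coefficient is not the fold change in the hypothesis. Section 2.4.5(e) leaves the choice open and so conflicts with it. The mismatch follows from the article's own definitions and needs no outside figures. The distortion of the effect (0.41, 0.18 or 0.11 in place of 0.69) assumes only the log link and the illustrative baselines.

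The power consequence is conditional: from almost none to almost unchanged, on assumed means and SDs. The stated 80% power at 168 should not be read as applying to ΔCT over the whole range 1.1 to 4.5. Under a linear model with equal groups and two-sided 0.05, power at fold change 1.1 is 43% at an assumed SD of 0.5 and 14% at SD 1, while twofold changes are well covered at SDs up to 2. Because this concerns the primary endpoint's model and the basis for the sample size, it should be settled before the analysis.

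**What to change.** - In sections 2.4.1 and 2.4.5(e), name a Gaussian linear model on ΔCT, with robust standard errors if needed, as the primary miRNA model. Remove the negative binomial option for this endpoint and keep it only for outcomes that are true counts.
- Report the fold change as 2^(−β) with its confidence interval, where β is the adjusted difference in mean ΔCT, exposed minus reference.
- Restate the power, or the minimum detectable fold change, for the planned sample from a stated ΔCT SD, alpha, group split and one minimum fold change. With 84 per group, two-sided 0.05 and 80% power, the detectable shift is about 0.43 SD, that is a fold change of about 1.35 at an assumed SD of 1 and 1.82 at SD 2.

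The cost is wording in two sections and one repeated calculation. It needs no further data and no change to recruitment.
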